## Methods

### Study design

This two-arm randomised controlled trial will involve men or women with a previous diagnosis of breast, colorectal or prostate cancer. All participants and peer supporters will first complete 4 weeks (12 sessions) of HIIT supervised by Accredited Exercise Physiologists (AEP) at the School of Human Movement and Nutrition Sciences, The University of Queensland, Brisbane, Australia (‘supervised phase’). On completion of the supervised phase, participants will be stratified by gender and age before being randomly assigned (1:1) to either a peer support group or a non-peer support group. All will be provided with written recommendations to maintain three HIIT sessions per week, or an alternative equivalent that meets the exercise oncology guidelines (i.e. 150 min per week of moderate or 75 min per week of vigorous aerobic exercise or an equivalent combination), for 12 months [21, 22]. Those assigned to the peer support group will have access to a peer who will provide support to meet the HIIT and/or exercise guidelines.

All participants will complete a series of assessments (see Table 1) at baseline, at the end of the supervised phase, and at 3-, 6- and 12-months following the supervised phase (see Fig. 1).

**Table 1 Tab1:** Schedule of data collection

Assessment or Outcome	Study Period						
*Time Point:*	*Pre-FM*	*FM*	*Pre-SP*	*Post-SP*	*3 M*	*6 M*	*12 M*
*Screening*							
Participant eligibility	✓						
Adult Pre-Exercise Screening System	✓						
Informed consent	✓						
Doctor’s consent	✓						
Medical history and current status	✓	✓	✓	✓	✓	✓	✓
Demographics	✓						
Concomitant research study participation	✓	✓	✓	✓	✓	✓	✓
*Primary Outcomes*							
Moderate-to-vigorous physical activity (MVPA)			✓	✓	✓	✓	✓
*Secondary Outcomes*							
Cardiorespiratory fitness ($$ \dot{\mathrm{V}}{\mathrm{O}}_{2\mathrm{peak}} $$)		✓	✓	✓	✓	✓	✓
Body composition (DXA)			✓	✓	✓	✓	✓
Anthropometry (BMI)			✓	✓	✓	✓	✓
Strength (isometric grip strength)			✓	✓	✓	✓	✓
Blood biomarkers (IL-6, IL-8, Hepcidin, TNF-α, IGF-1, IGF-2, IGFBP-3 and CRP)			✓	✓	✓	✓	✓
Self-reported physical activity (Godin)			✓	✓	✓	✓	✓
Sedentary behaviour and light physical activity (accelerometry)			✓	✓	✓	✓	✓
Quality of life and wellbeing (EORTC QLQ C-30, SF-36 and FACT-G)			✓	✓	✓	✓	✓
Cancer-related fatigue (FACIT-F)			✓	✓	✓	✓	✓
Insomnia (ISI)			✓	✓	✓	✓	✓
Symptom distress (BSI)			✓	✓	✓	✓	✓
Depression and anxiety (DASS, PHQ-9 and GAD-7)			✓	✓	✓	✓	✓

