### Randomisation

Following completion of the 4-week supervised training phase and the second testing session, participants will be stratified by sex and age before being randomly assigned (1:1 allocation ratio) to either a peer support group or a non-peer support group. Randomisation will be performed using a computerised random number generator by a research officer independent to the study. Non-systematic block sizes of four, six, or eight will be used to ensure allocation concealment. Randomisation history will be kept secure by the independent research officer in an electronic password-protected file. The independent research officer will confidentially communicate the allocation result to the trial’s primary investigator within 48 h after completing outcome testing following the second testing session. All investigators will be blinded to group allocation for baseline testing, the supervised phase and for testing following the supervised phase, with randomisation occurring after the completion of testing following the supervised phase. The primary outcome will be analysed by a researcher blinded to group allocation. Unblinding will not be permissible under any circumstances. A schematic representation of the study protocol is shown in Fig. 1.

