### Outcomes

Primary and secondary outcomes will be measured at baseline, at the end of the 4-week supervised phase, and at 3-, 6- and 12-months following the supervised phase. See Table 1 for a visual representation of the data collection schedule.

Assessments will be performed in a consistent order to allow for appropriate rest periods and to ensure that successive outcomes are minimally influenced by accumulative testing-fatigue. Participants will be advised to take prescribed medications as normal throughout the study period. Concomitant study participation will be documented at each testing session and the primary investigator will determine whether any co-intervention bias may influence the trial outcomes. Hospital admissions and any alterations in medical status or medications will be recorded at each assessment for future reference during analysis of results.

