### Primary outcome

#### Moderate-to-vigorous physical activity

The primary outcome for this study will be MVPA at 12 months. MVPA can be accrued through performance of the prescribed HIIT sessions and/or by engaging in any MVPA. Daily physical activity will be assessed through the use of training diaries, retrieval of HR and Wattbike ergometer data from each training session, as well as Actigraph GT3X+ accelerometry (Pensacola, Florida). Participants will be asked to wear an accelerometer on an elastic waist belt aligned with the right anterior axillary line for 7 days immediately preceding baseline, 3-, 6- and 12-month assessments. Participants will be asked to complete a brief log to record when they wear the monitor, including wake and sleep times and if they removed the monitor for > 10 min. They will be instructed to wear the device at all times, excluding sleep, any water-based activities (e.g. showering/swimming) and contact sports. Accelerometers will be initialised with 30 s epochs and a 30 Hz sampling frequency. A valid day will be defined as a minimum wear-time of 10 waking hours, with non-wear time defined as 60 min or more of consecutive activity counts of zero. For activity data to be included, participants must satisfy a minimum wear-time criterion of at least four of the 7 days, with at least one of the days being a weekend day [44, 45]. Minutes of MVPA will be calculated using Actilife v6 (Pensacola, Florida) and the cutpoints described by Troiano et al. [44].

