#### Physical activity preferences

The physical activity preference questionnaire will be used to assess the physical activity context preferred by participants throughout the duration of the trial due to its potential role as a covariate [109]. The questionnaire assesses physical activity preferences for 14 contexts of format (e.g. vigorous), location (e.g. outdoors), and social setting (e.g. done alone). Participants will be asked to provide ratings that reflect their agreement with one of two bi-polar statements at each end of the continuum (e.g. ‘Strongly disagree’ – ‘Strongly agree’) [110].

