### Statistical considerations and data analysis

A priori power calculations determined that a sample of *n* = 188 (*n* = 94 per group) will be needed to detect a minimum between-group difference in MVPA levels at 12 months, with 80% power and 5% alpha. To account for an anticipated dropout rate of 20%, 226 participants (*n* = 113 per group) will thus be recruited for this study. A priori criteria for successful provision of peer support will be contacting participants on average on one or more occasions per week over the 12-month maintenance phase.

Data will be assessed for normality of distribution using the Kolmogorov-Smirnov test. Raw continuous data (e.g. minutes of MVPA per day) will be analysed using linear mixed (fixed and random) modeling, to assess changes over time and differences between groups. Group, time, and group × time interaction will be treated as fixed factors; participants will be treated as a random factor with individual intercepts. Each model will include covariates, as appropriate, and will be adjusted using the baseline value as a fixed continuous covariate as previously described by Courneya et al. [113]. Model residuals will be formally assessed for normality by use of the Kolmogorov-Smirnov test and visual inspection of histogram plots. Bonferroni pairwise adjustments will be made for all subsequent comparisons.

Non-continuous data will be analysed with the target distribution and relationship fixed to multinomial logistic regression. Statistical significance will be set at an alpha of *p* < .05 and analyses will be conducted using the intention-to-treat approach. There are no interim analyses planned or early trial termination guidelines. Data from the peer supporters will be analysed separately to those of the participants.

Qualitative data from the semi-structured interview transcripts will be assessed using inductive thematic analysis. Codes will be assigned to salient text segments across the entire data set, before codes will be combined to define overarching themes [108].

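### MVPA at the last visit before randomisation is scheduled in Table 1 but missing from the accelerometer instructions, and the stated model gives it no role

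*Protocol article*

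**What the plan says.** **Schedule.** The Outcomes section states: "Primary and secondary outcomes will be measured at baseline, at the end of the 4-week supervised phase, and at 3-, 6- and 12-months". Table 1 (Study design) agrees, with MVPA ticked at five visits: pre-supervised, post-supervised, 3, 6 and 12 months. The Abstract also lists an assessment after the 4-week phase. The Moderate-to-vigorous physical activity section, which tells staff when the device is worn, gives four periods: "for 7 days immediately preceding baseline, 3-, 6- and 12-month assessments". Sedentary behaviour and light activity use the same accelerometer method and are also ticked at the post-supervised visit, so they inherit the conflict.

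**Randomisation.** Allocation comes after the second test session, "with randomisation occurring after the completion of testing following the supervised phase". The Randomisation and Outcomes sections list baseline separately from post-supervised testing, so baseline means the pre-training visit.

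**Model.** Statistical considerations and data analysis fits group, time and their interaction as fixed factors with a random participant intercept. Each model is "adjusted using the baseline value as a fixed continuous covariate", with further unnamed covariates where appropriate. The levels of time are not listed. The Abstract makes the group x time interaction the formal test at alpha 0.05.

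**Time point.** "The primary outcome for this study will be MVPA at 12 months".

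**The concern.** The question is whether activity is maintained after a supervised phase. Under Peer support intervention, the peer's goal is to hold activity at the level reached in that phase. The visit that records this level, immediately before allocation, is the one on which the schedule disagrees with itself. A pre-randomisation measurement that was not taken cannot be recovered later.

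If it is taken, the analysis section does not say what it is for. It could be a covariate, which would gain precision. It could instead be one of the levels of time, which changes what the group x time term tests. A reader of the protocol cannot tell which.

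**Working it through.** **1. Schedule, side by side**

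| Place | Pre-supervised | Post-supervised | 3 m | 6 m | 12 m |
|---|---|---|---|---|---|
| Table 1, MVPA row | yes | yes | yes | yes | yes |
| Outcomes section | yes | yes | yes | yes | yes |
| MVPA section, accelerometer wear | yes | no | yes | yes | yes |

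Diaries and ergometer records cover training sessions, but minutes of MVPA are calculated with the accelerometer software and cutpoints. The conflict therefore concerns the primary measure itself.

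**2. Precision.** The protocol gives no correlation between visits, so these are assumptions. Take an equal correlation r between pre-supervised, post-supervised and 12-month MVPA. Residual variance as a fraction of total is 1 - r² with one covariate and 1 - 2r²/(1 + r) with two.

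| r | Pre only | Pre and post | Variance cut | Equivalent gain in participants |
|---|---|---|---|---|
| 0.4 | 0.840 | 0.771 | 8% | 0.840/0.771 = 1.09, 9% |
| 0.5 | 0.750 | 0.667 | 11% | 0.750/0.667 = 1.125, 12.5% |
| 0.6 | 0.640 | 0.550 | 14% | 0.640/0.550 = 1.16, 16% |
| 0.7 | 0.510 | 0.424 | 17% | 0.510/0.424 = 1.20, 20% |

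With unequal correlations a (pre, 12 m), b (post, 12 m) and c (pre, post), R² = (a² + b² - 2abc)/(1 - c²).
- 0.4/0.4/0.6: R² = 0.128/0.64 = 0.20. Residual variance falls from 0.84 to 0.80, a 5% cut.
- 0.5/0.7/0.6: R² = 0.32/0.64 = 0.50. Residual variance falls from 0.75 to 0.50, a 33% cut.

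**3. What the group x time test measures.** The protocol states 94 per group, 80% power and 5% alpha but no difference or SD, so its 188 cannot be rebuilt from inputs. For two means, two-sided, 94 per group implies a standardised difference d = (1.960 + 0.842) x √(2/94) = 0.409.

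Assume this d is constant at 3, 6 and 12 months, and that residual correlation ρ is the same between all visits. The noncentrality of the interaction test is (94/2) x d² x S/(1 - ρ), where S is the sum of squared deviations of the visit effects from their mean.

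- *Post-supervised visit as a level of time:* effects 0, 1, 1, 1 give S = 0.75, on 3 degrees of freedom. Noncentrality is 8.41, 11.77 and 19.62 for ρ = 0.3, 0.5 and 0.7. Power is 68%, 83% and 97%.
- *Only 3, 6 and 12 months as levels:* effects 1, 1, 1 give S = 0. Power is 5%, that is, alpha.
- *Group effect averaged over all four levels:* (0 + 1 + 1 + 1)/4, three quarters of the true effect.

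**4. The 12-month contrast at the same d.** With r = 0.5 throughout and 94 per group, power is 89.9% adjusting for the pre-supervised value and 92.9% adjusting for both values.

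**The case against.** **What stands.**
- All sections agree on the 12-month measurement, so the primary time point is not in doubt.
- The analysis section does not list the levels of time and allows other covariates. A reader might infer that the plan definitely analyses the post-supervised visit as follow-up, or that it excludes the post-supervised value and the strata. The text supports neither. If the accelerometer wording governs, there is no post-supervised MVPA level at all.
- A reader might infer bias from adjusting for a pre-training value. Randomisation rules that out, and chance imbalance at the post-supervised visit affects precision only.
- Calling the post-supervised value the best predictor of later activity has no support in the document. A 7-day window just before that test probably overlaps the last supervised week and may not reflect self-directed activity.
- The preference questionnaire is collected "throughout the duration of the trial due to its potential role as a covariate". A reader might infer that a post-randomisation score will be adjusted for. Table 1 also ticks it at both pre-randomisation visits, and nothing commits to a later value.
- Keeping the post-supervised visit as a level of time is not simply harmful. It gives the interaction a reference point at randomisation, and with a constant effect it is where the interaction's power comes from. Removing that level without changing the test would be a mistake.

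**What does not stand.** A separate analysis plan could settle the model, but it cannot resolve a contradiction within the protocol about when the primary measure is collected.

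**Conclusion.** The point holds as a contradiction in the schedule of the primary measure, together with an undefined role for the last value before randomisation. It is a matter of precision and clarity, not of bias.

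The gain from using the post-supervised value is 8 to 17% of residual variance, or about 9 to 20% more participants, under assumed equal correlations of 0.4 to 0.7. The unequal patterns tried widen the variance cut to 5 to 33%. Under a constant effect of 0.409 SD, the group x time test has power between 68% and 97% with the post-supervised visit as a level, and 5% without it. The correlations and the constant effect are assumptions. The dependence of the stated test on an unspecified choice does not rest on their exact values.

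**What to change.** 1. Reconcile the accelerometer wording in the MVPA section with Table 1 and the Outcomes section so that the device is worn for the post-supervised assessment. Define that wear window explicitly, because it may overlap supervised sessions. The same correction then covers sedentary behaviour and light activity.
2. Use 3, 6 and 12 months as responses, with the pre-supervised and post-supervised values and the sex and age strata as covariates.
3. Make the 12-month between-group contrast from this model the primary test, in place of the overall group x time interaction. This matches the stated primary time point. Steps 2 and 3 must go together, because the interaction over 3, 6 and 12 months has almost no power against a constant effect.
4. If activity preference is used as a covariate, take a value measured before randomisation.

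**Cost.** If Table 1 has been followed, this is wording only. If staff have been following the MVPA section, one added wear period is a small operational change. Some participants will lack a post-supervised value and need simple baseline imputation. That keeps them in the model but cannot restore the precision of a value that was not collected.

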#### Depression and generalised anxiety (PHQ-9)

Depression is highly prevalent among people with cancer, with rates of depressive spectrum disorders as high as 58% [95]. The Patient Health Questionnaire-9 (PHQ-9) is a multipurpose instrument that will be used to assess severity of depression [96]. The diagnostic validity of the PHQ-9 was established in studies involving eight primary care and seven obstetrical clinics. PHQ scores ≥10 had a sensitivity of 88% and a specificity of 88% for major depression [96, 97]. PHQ-9 scores of 5, 10, 15, and 20 represents mild, moderate, moderately severe and severe depression [98].

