#### Participant:peer supporter relationship

The quality of the bond between the peer-supporters and their participants will be assessed using an adapted version of the Working Alliance Inventory (WAI) questionnaire [101]. The WAI is a 7-point Likert-type measure that assesses 12 alliance dimensions including ‘agreement on task’, ‘agreement of goals’ and ‘development of bonds’, amongst others [102, 103]. The WAI has demonstrated high construct validity and high internal consistency estimates [103]. The WAI has been adapted for terminology relevance regarding ‘HIIT’ and ‘peers’ in this study. Furthermore, the 7-point Likert scale has been condensed to a 5-point Likert scale for consistency and ease of interpretation with the other study questionnaires.

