#### Self-efficacy

To assess self-efficacy beliefs, participants will review the exercise recommendations for this trial (3 x HIIT sessions per week), and indicate the extent to which they feel capable of successfully adhering to these recommendations. Specifically, participants will be asked to what extent they would rate the truth of the statement ‘I feel capable of successfully completing 3 x HIIT sessions per week for 4 weeks, 3 months, 6 months, 9 months, and 12 months’, respectively. Participants will be asked to rate their responses on a 5-point Likert scale ranging from ‘strongly disagree’ to ‘strongly agree’. This method of assessing self-efficacy has been adapted from the Self-Efficacy for Exercise (SEE) scale which was originally described and validated in older adults by Resnick & Jenkins [104].

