#### Barriers and enablers to exercise participation

Barriers and enablers to exercise participation will be assessed via two open-ended written questions about barriers and enablers to physical activity/exercise, as described by Evenson et al. and Macniven et al. [105, 106]. The barrier question will ask: ‘What is the one main reason that makes it harder for you to be more active?’. The enabler question will ask: ‘What is the one main reason that helps you to be more active?’. Two investigators will code responses and any discrepancies will be resolved by consensus. These items will be grouped into meaningful categories considering the socioecological framework, with intrapersonal, interpersonal, neighborhood or environmental, and organizational or policy categories.

Participants will also be asked to provide statements based on the Behavioural Regulation in Exercise Questionnaire Version 2, as previously used by Martin et al. and Markland et al. [24] [107]. Participants will be asked to respond to matrix-based questions such as ‘I find it difficult to exercise because of fatigue’ and ‘I am motivated to perform exercise because it will improve my physical health’. Participants will rate their agreement with the statements on a 5-point Likert scale ranging from ‘strongly disagree’ to ‘strongly agree’.

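### If the 5-point ratings are analysed as categories, the fixed multinomial logistic model would ignore their order and weaken the group comparison

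*Protocol article*

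**What the plan says.** The section Statistical considerations and data analysis of the protocol article splits outcomes in two. Continuous data go to a linear mixed model, for which "Group, time, and group × time interaction will be treated as fixed factors", with a random intercept per participant. For the rest, "Non-continuous data will be analysed with the target distribution and relationship fixed to multinomial logistic regression". The section does not list which outcomes count as non-continuous, makes no exception for ordered data and names no link function.

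Two secondary outcomes are defined as single ordered items:

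- **Self-efficacy.** "Participants will be asked to rate their responses on a 5-point Likert scale", running from strong disagreement to strong agreement, once for each of five time horizons. No sum score is described.
- **Barrier and motivation statements.** "Participants will rate their agreement with the statements on a 5-point Likert scale", with the same end points.

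The section Barriers and enablers to exercise participation also has two open-ended questions whose answers are coded: "These items will be grouped into meaningful categories considering the socioecological framework". Those categories have no order.

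On timing, the Outcomes section says "Primary and secondary outcomes will be measured at baseline, at the end of the 4-week supervised phase, and at 3-, 6- and 12-months". Randomisation follows the second of these assessments, so three visits come after it.

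**The concern.** In its ordinary sense, multinomial logistic regression treats the levels of an outcome as unordered labels and estimates a separate group contrast for each non-reference level. For an agreement rating this discards the information that agreement lies above neutrality and neutrality above disagreement. Two things follow:

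- The evidence for peer support is spread over several parameters, so the overall test is less powerful when the effect is a general shift up the scale.
- The report contains several contrasts per item and no single statement of how far peer support moved the rating.

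Self-efficacy is one of the things the peer supporters are trained to build (sections Recruitment and training of peer supporters, and Peer support intervention), so a blunt analysis of it would be a real, though secondary, loss.

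This is more than detail left to an analysis plan. The article states a rule, and an analysis plan that follows it for ordered ratings inherits the weakness.

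**Working it through.** **No figure of the plan to reproduce.** The article gives no degrees of freedom, power or sample size for any non-continuous outcome. Its only sample-size figures concern MVPA. From them I take 94 evaluable participants per arm, 1:1 allocation, 5% alpha (two-sided assumed) and 80% power as the reference level.

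**Step 1: degrees of freedom.** Let K be the number of levels and T the number of post-randomisation visits. I assume that the fixed terms stated for the linear mixed model carry over.

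- Group effect: 1 in a cumulative-logit model; K − 1 in a generalised-logit model. With K = 5: 1 against 4.
- Group by time: T − 1 against (K − 1)(T − 1). With K = 5 and T = 3: 2 against 4 × 2 = 8.

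The ratio is K − 1: 4 for five levels, 3 for four, 2 for three and 1 for a binary outcome.

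**Step 2: power at equal information.** Under proportional odds the two models share approximately the same non-centrality λ, and power = P(χ²(df, λ) > χ²₀.₉₅(df)).

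- Group effect: 80% power on 1 df needs λ = 7.85. The same λ on 4 df gives 59.5%.
- Group by time: 80% power on 2 df needs λ = 9.63. The same λ on 8 df gives 56.8%.
- Restoring 80% would take 1.52 times the sample on 4 df (λ = 7.85 × 1.521 = 11.94) and 1.56 times on 8 df (λ = 9.63 × 1.559 = 15.0).

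With fewer levels the group-effect figure is 64.5% for four levels, 70.9% for three and 80% for two, that is, no loss for a binary outcome.

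**Step 3: simulation check.** I ran 2,000 simulated trials per setting, with 94 per arm, one visit, five levels and likelihood-ratio tests on 1 and 4 df. The odds ratios and category spreads are assumptions, because the article gives none. Even means 20% in each level; skewed means 5, 10, 20, 40 and 25%.

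| Spread | Odds ratio | Ordinal | Multinomial |
|---|---|---|---|
| Even | 2.0 | 76% | 54% |
| Skewed | 2.0 | 73% | 52% |
| Even | 2.1 | 81% | 64% |
| Skewed | 2.1 | 78% | 58% |

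With no effect, the rejection rate was 5.0% for the ordinal test, and 4.9% (even) and 6.3% (skewed) for the multinomial test. The loss of 17 to 22 points agrees with the analytic figure of about 20.

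**The case against.** The best defence is that the article never assigns the 5-point ratings to this model. It does not say which outcomes are non-continuous, and the ratings could be scored or summed and sent to the linear mixed model. The one outcome that is plainly categorical, the coded open-ended reasons, is nominal, and multinomial regression suits it. Nor does the sentence name a link: a multinomial distribution with a cumulative logit would keep the order. All of this stands, and it makes the concern conditional. It does not remove it. Single 5-point items without a sum score are natural candidates for non-continuous data, and generalised logits are the ordinary meaning of the method named. If an ordinal link was meant, the sentence still needs to say so.

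Several stronger readings may tempt a reader, and the documents do not support them:

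- **That every non-continuous outcome is harmed, at four times the degrees of freedom.** The factor of four belongs to five-level ordered items only.
- **That depression severity grades are affected.** The article says "PHQ-9 scores of 5, 10, 15, and 20 represents mild, moderate, moderately severe and severe depression", but this describes the instrument; nowhere are the grades named as an analysed endpoint.
- **That the working-alliance items add to the case.** There "the 7-point Likert scale has been condensed to a 5-point Likert scale", but the article does not say whether items are summed, and a control participant has no peer supporter to rate.
- **That sparse levels will give unstable or infinite estimates.** No response distribution is given for any item.
- **That self-efficacy is the mechanism of the intervention.** It is listed beside motivation, confidence, goal setting and overcoming barriers.

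**Conclusion.** The point holds in conditional form. If the self-efficacy ratings and the barrier and motivation statements are analysed as categories with generalised logits, the stated rule costs 3 extra degrees of freedom for a group effect and 6 for group by time, and it leaves no single effect to report. The fall from 80% power to about 60% or 57% is an illustration. It rests on proportional odds, on 80% power in the ordinal model (which the trial does not claim for these outcomes), and on fixed terms that the article states only for continuous data. If odds are not proportional, the loss shrinks and may reverse.

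A reader might infer that the trial's main conclusion is at risk. It is not: MVPA is analysed by the linear mixed model, and only secondary outcomes are touched. This is a cheap improvement, not a flaw that threatens the trial.

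**What to change.** Replace the sentence on non-continuous data with a rule by outcome type, and list which outcomes fall under each:

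- **Ordered ratings analysed as categories:** a cumulative-logit (proportional-odds) mixed model with group, time, group by time and a participant random intercept, reporting one odds ratio per visit. Check proportional odds, with a partial proportional-odds model as the named fallback.
- **Binary outcomes:** logistic mixed models.
- **Coded, unordered barrier and enabler reasons:** multinomial logistic regression, as now.

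For each 5-point rating, state whether it is analysed as ordered categories or scored as continuous. Settle this before any analysis by group, so that the model is not chosen after seeing results.

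The cost is wording in the analysis plan, with no new data or participants. The one downside is the work of checking the proportional-odds assumption.
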